### 2.4. Participants

#### 2.4.1. Inclusion Criteria

(1)Obesity diagnostic criteria: waist circumference ≥ 80 cm and BMI ≥ 25 are the criteria listed in the Comprehensive Medical Management Guidelines for Obese People jointly published by the American Society of Clinical Endocrinologists (AACE) and the American College of Endocrinology (ACE) in May 2016 [28](2)Menopausal syndrome diagnostic criteria: refer to “Obstetrics and Gynecology” [29]and the China Association for Traditional Chinese Medicine's recommendations for the diagnosis and treatment of menopausal syndrome in 2020 [30]:① women's age is 40–60② The menstruation is out of the regularity, and the menstrual cycle appears >7 days, but <2 months, or the menopause time >2 months, rule out the menopause caused by other reasons③ There are manifestations of menopausal syndrome with kidney Yin and Yang deficiency: before and after menopause, menstrual disorders, dark or light red menstruation, sometimes hot, sometimes chills; spontaneous sweating, night sweats, dizziness, tinnitus, insomnia, forgetfulness, cold back pain, heel pain, swelling, loose stools, frequent urination; pale tongue, white fur, heavy, and weak pulse④ Serum FSH>10IU/L(3)Having not used any hormone-related or weight-loss-related medications in the previous 3 months(4)Being the ability to fully comprehend and willingly sign informed consent

#### 2.4.2. Exclusion Criteria

Unexplained vaginal bleeding, or unnatural menopauseHistory of using hormone replacement treatment or other medications for the condition within the previous 3 monthsRespiratory illnesses, heart, liver, and renal problems, as well as severe organic and endocrine diseasesHypothalamic lesions, hypothyroidism, glucocorticoid medication, and other conditions can produce secondary obesityOrganic illnesses of the uterus, such as polycystic ovary syndrome, malignant tumors, severe cervical erosion following complete hysterectomy, and so forthContraindications to moxibustion include moxibustion intolerance, skin allergies, scarring, and other significant skin illnessesInability to adhere to therapy due to poor compliance

#### 2.4.3. Withdrawal from the Study

Pregnancy or other diseases are found during treatment, or serious adverse reactions and complications occur, and a specialist physician at each center decides to terminate the patient's participation in the trialCombines the treatment methods prohibited by this study or changes the specified treatment method halfwayPoor compliance and unable to implement treatment in accordance with the prescribed test protocolParticipant's decision to withdraw from the study

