## Abstract

*Background*. In the past, moxibustion has been widely used to treat endocrine system disorders, but evidence of its effectiveness is scarce at this point. The aim of this multicenter, randomized, controlled trial is to evaluate the efficacy and safety of treating menopausal obesity with moxibustion. *Methods/Design*. There are six centers taking part in this randomized, controlled, parallel trial. A total of 216 patients with menopausal obesity will be randomly divided into two equal groups: the “moxibustion for harmonization of Yin and Yang” group and the gentle moxibustion group. A 12-week study period with moxibustion will be preceded by a 1-week baseline, followed by a 12-week follow-up. We will conduct an interim analysis to determine whether or not the treatment is efficacious and safe after 216 participants have completed a 12-week treatment period. Evaluations will be conducted at weeks 0, 4, 8, 12, 18, and 24. The main outcome is waist circumference (WC), and the rate of WC reduction will be compared to the baseline. An intention-to-treat analysis will be performed with a two-sided *P* value of <0.05 considered significant. Participants who withdraw from the trial will be analyzed according to the intention-to-treat formula (ITT). *Discussion*. These results will be used to support selecting the right moxibustion prescription and guiding the improvement of clinical efficacy. This trial will provide convincing evidence of moxibustion's effectiveness and safety in the treatment of obesity by “moxibustion for harmonization of Yin and Yang,” which will be conducive to the promotion and clinical application of the theory of “moxibustion for harmonization of Yin and Yang.” *Trial Registration*. This trial is registered with Clinical Trials.gov: NCT04943705 (registered on June 27, 2021).

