### 2.2. Study Design

This will be a multicenter, randomized, controlled, two-arm clinical trial, where 216 participants will be randomized at a ratio of 1 : 1 to two groups (108 participants per group). There are six academic hospitals in China where this study will be carried out: Hubei Provincial Hospital of TCM, Shanxi Provincial Hospital of TCM, Shenzhen Baoan Hospital of TCM (Group), Xiamen Hospital of TCM, Jiangsu Provincial Hospital of TCM, and the First Affiliated Hospital of the Hunan University of TCM. A 12-week treatment phase plus a 12-week follow-up period make up the 24-week duration of this research. If they are qualified for the study, each participant is required to keep a diet and exercise diary for the whole research cycle. All participants will receive 12 weeks of individual treatments in two groups: the “moxibustion for harmonization of Yin and Yang” will be administered once every 1 week, 60 minutes each time; the gentle moxibustion will be administered 3 times a week, 20 minutes each time. Outcomes will be assessed at the beginning, at the conclusion, and during the follow-up period. The Standard Protocol Items: Recommendations for Intervention Trials (SPIRIT) [26] are utilized in the protocol, which is based on the Standards for Reporting Interventions in Clinical Trials of Acupuncture (STRICTA) [27](Additional file 1).  Figure 1 provides a summary of the trial's design.

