### 2.6. Blinding

Throughout the study, participants will be kept in the dark about their group assignment. They will listen to an explanation that they will undergo “moxibustion for harmonization of Yin and Yang” or “gentle moxibustion.” The assessor, data recorder, acupuncturist, and statistician will all work independently; the randomization staff and acupuncturist will be aware of the allocation information, but the assessor and statistician will stay blind to it throughout the trial. To avoid the interchange of study information, each participant will be treated independently. In the event of withdrawal, the study research assistant would present the participant with the pertinent information, which would include the individual's treatment assignment and outcome data.

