### 2.11. Statistical Analysis

SAS 9.3 software will be used by an impartial statistician to analyze the data (SAS Institute Inc, Cary, NC). Any participant who completes the randomized stage and receives at least one intervention will be analyzed using a full analysis set (FAS), with missing data for the important outcomes interpolated with the last observation carried forward, in accordance with the intention-to-treat (ITT) analysis strategy. Multiple imputations will be used to deal with missing data. All statistical inspections were used for bilateral testing, and statistical significance will be determined at *P* < 0.05.

For the patient's missing data, it is assumed that the deletion data is randomly missing, the lacking value of the research main indicator is used for multiple filling methods, the stochastic missing deletion assumption of multiple filling is performed, and the stability test of the missing data filling results is carried out by using pattern mixture model (PMM). The measurement data is described by average ± standard deviation ($\bar{x}\pm S$), median, maximum, and minimum, and the counting data and grade data are described by cases and percentages. Intergroup comparison will select the analysis method according to the data distribution feature: the measurement data is used to test or nonparameter testing; the count data is used in*χ*^2^inspection or Fisher's exact probability method, and the grade data is used in the nonparameter test. Compared with the baseline value, the metering data is used in pair*T*inspection or nonparameter test, and counting materials use nonparameter test.

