### 2.13. Quality Control

The acupuncture, methodology, and statistics specialists examine and make revisions to the study protocol. A predetermined standard operating procedure will be used to teach the relevant employees. Through health education and prompt follow-up, patient compliance will be increased. If the subjects stop using moxibustion or depart from the procedure, the results will also be assessed by outcome assessors. This study will carry out a central randomization system to prevent bias in selection. At the same time, one of the most crucial strategies for preventing bias is the careful selection of inclusion and exclusion criteria, contributing to the objectivity of conclusions. A third-party blinded method will be applied to this study, namely, for assessing efficacy and safety by assessors who are not familiar with the group characteristics. To ensure the smooth progress of the study, all clinical researchers will be trained in the SOPs about moxibustion before the study begins to improve the consistency of researchers' and spectators' internal observations, in order to guarantee the validity of the conclusions. We will conduct sensitivity analyses in the per-protocol set. During this study, we will hold regular multicenter team meetings and go through routine checks to prevent center bias.

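### Section 2.4.3 withdraws non-compliers, switchers and users of prohibited treatment from the study, while section 2.13 says those who depart from the procedure are still assessed; the two must be reconciled

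*Protocol article*

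**What the plan says.** Section 2.4.3 of the protocol article is headed "Withdrawal from the Study". One item is poor "compliance and unable to implement treatment in accordance with the prescribed test" protocol; another covers a participant who combines "methods prohibited by this study or changes the specified treatment" method partway through. They stand in one list with medical events that lead a physician to end participation and with the participant's own decision to leave. The section does not say whether outcome visits continue.

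Section 2.6 describes what follows withdrawal: "In the event of withdrawal, the study research assistant would present the participant with the pertinent information", and this includes her own assignment and outcome data. The same section says that participants are kept unaware of their group throughout the study.

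Section 2.13 states: "If the subjects stop using moxibustion or depart from the procedure, the results will also be assessed by outcome assessors".

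On the analysis, the Abstract says: "Participants who withdraw from the trial will be analyzed according to the intention-to-treat formula (ITT". Section 2.11 agrees: "Any participant who completes the randomized stage and receives at least one intervention will be analyzed using a full analysis set (FAS". For missing values it names both last observation carried forward (LOCF) and multiple imputation under a missing-at-random assumption, with a pattern mixture model as a stability check. Section 2.13 uses the per-protocol set for sensitivity analyses only.

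**The concern.** A participant who misses many sessions, or who turns to another weight-loss treatment, meets a withdrawal criterion in 2.4.3 and is also someone who has departed from the procedure under 2.13. Staff at six centers have no rule telling them which section governs, so whether her remaining waist measurements are taken may vary by center.

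If 2.4.3 is followed as the end of participation, the missing values do not arise by chance. They belong to participants picked out by what they did after randomisation, and that behaviour is plausibly tied to response: someone who is not losing waist circumference has more reason to stop attending or to try something else. An ITT analysis then keeps these participants in name, while their later values come from a model. Those values could have been measured.

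The attendance demand also differs by design. Section 2.2 says that "the gentle moxibustion will be administered 3 times a week, 20 minutes each time" for 12 weeks, against one session a week in the harmonization arm. Unequal withdrawal for poor compliance is therefore plausible, although nothing in the article documents it.

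**Working it through.** **Passages side by side**

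| Question | 2.4.3 with 2.6 | 2.13 |
|---|---|---|
| Participant complies poorly, switches, or uses prohibited treatment | Withdrawn from the study | Departed from the procedure |
| Outcome assessment afterwards | Not stated; disclosure of allocation and results suits an ended participation | Continues |
| Participant unaware of her group at later visits | No, once told | Needed if the 2.6 blinding is to last throughout the study |

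Membership of the analysis set is not in conflict: the Abstract and 2.11 keep withdrawn participants. The conflict is about data collection.

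**Inputs from the article**
- 108 per arm, 216 in total, 10% dropout with no split by arm (2.9). 0.10 × 216 = 21.6, about 22 participants. This figure covers all dropout, so it is an upper guide to the number affected by 2.4.3.
- Sessions: 12 × 1 = 12 (harmonization) and 12 × 3 = 36 (gentle). Treatment time is equal: 12 × 60 = 36 × 20 = 720 minutes.
- Planned difference: 6.15 − 3.94 = 2.21 cm. Pooled SD = √[(1.56² + 1.14²)/2] = 1.366 cm. Standardised effect = 2.21/1.366 = 1.62.

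The plan gives no figure for this point that could be reproduced. The rest is illustration. Withdrawal rates by arm and the gap D between completers and withdrawn participants are assumptions.

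**Case A: values filled from completers in the same arm**

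Each arm's mean is overstated by p × D, so the bias in harmonization minus gentle is (p_harm − p_gentle) × D. The standard error in SD units is √(2/108) = 0.136. Two-sided rejection under no true difference is P(|Z + bias/SE| > 1.96), by normal approximation and ignoring imputation variance.

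| Withdrawn, gentle / harmonization | D (SD) | Bias against harmonization (SD) | Rejection under the null | of which wrongly favours harmonization |
|---|---|---|---|---|
| 10% / 10% | any, same in both arms | 0 | 5.0% | 2.5% |
| 15% / 5% | 0.5 | 0.05 | 6.6% | 1.0% |
| 15% / 5% | 1.0 | 0.10 | 11.4% | 0.35% |
| 20% / 5% | 0.5 | 0.075 | 8.5% | 0.6% |
| 20% / 5% | 1.0 | 0.15 | 19.7% | 0.1% |

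The excess rejections favour gentle moxibustion.

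Power depends on the effect used:
- At the stated 1.62 SD, power stays at essentially 100% even with a bias of 0.15 SD (0.15 × 1.366 = 0.20 cm).
- At 0.406 SD, the effect for which 96 per arm gives 80% power, power with 108 per arm is 85% without bias, 74% with a bias of 0.05 SD and 61% with 0.10 SD. The plan does not state this smaller effect; it is back-calculated from the 96.

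**Case B: values carried forward**

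Suppose there is no true difference, a 3.94 cm reduction in both arms, and withdrawal at week 4 after one third of it. Each withdrawn participant is credited with 3.94 × 2/3 = 2.63 cm too little. With 15% (gentle) versus 5% (harmonization): (0.15 − 0.05) × 2.63 = 0.26 cm in favour of harmonization, the opposite direction from Case A.

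**The case against.** The strongest reply is that 2.4.3 never says visits stop. The only sentence on assessment after a deviation is in 2.13, and it says assessment continues. The sections can be read together, and a condensed article may leave off-treatment follow-up to the full protocol. This stands in part: the loss of data depends on how centers read 2.4.3. But the issue is more than missing detail. The heading of 2.4.3, its neighbouring items and the disclosure in 2.6 all point to ended participation, and nothing gives 2.13 priority.

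A reader might infer that the plan abandons ITT. The documents do not support that: the Abstract and 2.11 retain withdrawn participants, and the per-protocol set serves sensitivity only.

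A reader might also infer that missingness will depend on arm. That is not documented either. There is one overall dropout figure, no compliance threshold, and equal treatment time in both arms.

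The plan also has a safeguard. The pattern mixture model can probe departures from missing at random, and multiple imputation can use a participant's own earlier waist values, so Case A is pessimistic where those values predict the outcome. Neither recovers a measurement that was not taken.

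Finally, telling a withdrawn participant her allocation does not by itself unblind the assessor, whom 2.6 keeps blind. That is correct. It does end her own blinding before any later visit under 2.13.

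**Conclusion.** The point holds as a conflict between 2.4.3 (with 2.6) and 2.13 that should be resolved before centers apply it. If 2.4.3 is read as ending participation, obtainable waist measurements are lost for a group selected after randomisation, at most about 22 of 216 at the planned dropout. The ITT result then depends on LOCF or missing-at-random imputation for them.

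The article does not fix the size or direction of any bias. The figures of 0.05 to 0.15 SD and 0.26 cm rest on assumed withdrawal rates and gaps. A claim that the primary conclusion would turn on this rule is not supported at the stated 2.21 cm effect; it would become a concern only if the true effect were much smaller. The change is still worth making, because it replaces assumptions with data at low cost.

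**What to change.** - In 2.4.3, leave the clinical criteria for stopping study moxibustion as they are, but state that stopping or departing from treatment is not withdrawal from follow-up. Reserve withdrawal from follow-up for participants who withdraw consent to further data collection.
- In 2.13 and 2.11, state that participants who comply poorly, switch, or use prohibited treatment keep their scheduled blinded waist assessments to week 24, and that their observed values are analysed in the arm to which they were randomised. Deviations define only the per-protocol sensitivity set. Impute only what could not be obtained.
- In 2.6, defer disclosure of allocation and outcome data until the participant's last assessment, unless it is needed for safety.

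The cost is protocol wording and some effort to retain deviating participants for visits that are already scheduled. The ITT difference may also come out slightly smaller, because non-compliers contribute their real values.

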### 2.5. Randomization and Allocation Concealment

To complete the randomization, we will utilize an online or messaging system run by a clinical information management system (Beijing Shuanghua Science and Technology Development Co, Ltd. China). When a subparticipant-recruiting center's staff accepts an eligible menopausal obesity patient, the patient's name, gender, age, and medical history are entered into the central randomization system. The acupuncturists will then be allocated a random number and an identity code that are unique to each participant. The allocation number will be kept secret from all participants.

### 2.6. Blinding

Throughout the study, participants will be kept in the dark about their group assignment. They will listen to an explanation that they will undergo “moxibustion for harmonization of Yin and Yang” or “gentle moxibustion.” The assessor, data recorder, acupuncturist, and statistician will all work independently; the randomization staff and acupuncturist will be aware of the allocation information, but the assessor and statistician will stay blind to it throughout the trial. To avoid the interchange of study information, each participant will be treated independently. In the event of withdrawal, the study research assistant would present the participant with the pertinent information, which would include the individual's treatment assignment and outcome data.

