### 2.3. Recruitment

we will create a public recruiting advertisement in newspapers, posters, WeChat, or the Internet and seek any patients who fit the requirements. Patients' eligibility to take part in this study will be decided by the doctor. Each patient will have enough time to decide whether or not to take part in the research. And each participant will be required to sign a freely completed written informed consent form. It informs patients about connected clinical research in terms that patients or their legal representatives may comprehend, including explanations of the study purpose, research technique, and procedure.

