#### 2.7.2. “Moxibustion for Harmonization of Yin and Yang” Group

Shenque (RN8) and Mingmen (DU4) will be chosen as acupoints (Figure 2). The acupoints are located in accordance with the national GB/T 12346–2006 acupoints standard [32]. Each treatment lasts 60 minutes once a week and alternates between “Wenyang Yishen moxibustion” and “Peiyuan Guben moxibustion.” For a total of 12 weeks, each patient received “WenYang Yishen moxibustion” followed by “Peiyuan Guben moxibustion.” The width and length of the patient's moxibustion site are measured using the same body measurement method before performing “Wenyang Yishen moxibustion.” We take about 700 g of fresh ground ginger with moderate dryness and wetness and shape it into a round cake with a diameter of about 20 cm and a thickness of about 2.5 cm on a sterile towel. We light 25 g of moxa with a diameter of about 18 cm on top of the ginger. When the bottom temperature reaches approximately 37°, the moxibustion materials can be applied to the patient's waist for treatment. The temperature should be kept between 43 and 45°, depending on the patient's tolerance. It is preferable to add the moxa after about 10 minutes of burning. When moxibustion occurs, there is a slight red burning heat in the patient's partial skin. Moxibustion takes 60 minutes. The operation of “Peiyuan Guben moxibustion” is the same as that of “WenYang Yishen moxibustion,” which is centered on Shenque. Moxa is selected from folium *artemisia argyi* from Qichun County, Hubei. We slice the fresh ginger and put it into a ginger grinder to crush it to make about 1 mm minced ginger. We take out the minced ginger and squeeze out the excess water to keep the ginger mud soft and moist. The humidity is controlled at 80–90% (measuring with a moisture tester). The prepared grated ginger is stored in a refrigerator at 4°C and heated in a microwave oven on medium-high heat for 5 minutes before applying moxibustion. During the moxibustion process, a digital thermometer will be placed between the sterile towel and the acupoint to control the moxibustion temperature.

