### 2.10. Data Monitoring and Management

Print and digital case report forms will be used to maintain all data (CRFs). Primary entries cannot be modified, and any corrections require a signature in the appended comments along with an explanation. CRFs are only accessible to outcome assessors, and duplicate data input will be done. All facets of the company are under the control of the Wuhan research team. Every month, this experiment and its results will be monitored by the Hubei Provincial Hospital of TCM's ethics committee, which will also ultimately decide whether to end the trial. Interventionists will keep an eye out for negative situations and respond properly with advice and encouragement. The protocol requirements must be understood and followed by all researchers, acupuncturists, and related personnel.

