### 2.12. Safety Assessment

Vital signs and adverse events will be considered in the moxibustion safety evaluation. Prior to randomization and after therapy, a general physical examination using safety indicators such as blood pressure, heart rate, respiration, pulse, and body temperature will be performed. Aside from that, the frequency of adverse events, including moxibustion burns, blistering, dizziness, ulceration, infection, local abscess, irregular vaginal bleeding, fatigue, allergies, and anorexia will be meticulously recorded in the CRFs and monitored by the Ethics Committees.

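### Section 2.6 claims participant blinding that two visibly different moxibustion regimens cannot deliver; the trial is at most assessor- and statistician-blinded

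*Protocol article*

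**What the plan says.** Section 2.6 makes an unqualified claim: "Throughout the study, participants will be kept in the dark about their group assignment". It then describes what participants are told: "They will listen to an explanation that they will undergo" one or other of the two treatments, each given by name. Section 2.3 says that consent covers the conduct of the study, "including explanations of the study purpose, research technique, and procedure".

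The regimens are set out in Sections 2.2 and 2.7. For the harmonization arm, Section 2.7.2 says: "Each treatment lasts 60 minutes once a week and alternates between" two forms, one applied at the waist and one centred on Shenque. For the comparator, Section 2.2 says: "the gentle moxibustion will be administered 3 times a week, 20 minutes each time".

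Section 2.6 says that the assessor and the statistician stay blind, while the acupuncturist and randomization staff know the allocation. Section 2.13 repeats that blinded assessors judge both efficacy and safety. Section 2.10 adds that "CRFs are only accessible to outcome assessors". Section 2.12 says that adverse events, burns and blistering among them, "will be meticulously recorded in the CRFs and monitored by the Ethics Committees".

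**The concern.** A woman who knows the names of the two treatments, and sees and feels which procedure she is given, knows her treatment in every sense that matters for expectation. Hiding an allocation number (Section 2.5) and treating women separately (Section 2.6) do not conceal the procedure itself.

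Two things are at stake. First, the secondary outcomes include IWQOL-Lite and SF-36, which are quality-of-life scales, and two symptom scores, the modified Kupperman and the TCM syndrome score. A reader who believes participants were blind would give differences on the self-reported scales more weight than they can bear. Second, waist circumference, the primary outcome, also responds to the diet and exercise that participants carry out and record themselves for 24 weeks (Section 2.7.1). Knowing which treatment one receives could change that effort.

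**Working it through.** No figure in the article quantifies blinding, so there is none to reproduce. The check sets the sections side by side.

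**1. Can a participant tell which procedure she receives?**

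| Feature | Harmonization arm (2.2, 2.7.2) | Gentle arm (2.2, 2.7.3) |
|---|---|---|
| Device | Ginger cake about 20 cm across, moxa burning on top | Lit moxa stick, 1.5 cm diameter, held 2–3 cm off the skin |
| Sites | RN8 and DU4 | RN12, RN4 and SP6 |
| Session length | 60 minutes | 20 minutes |
| Sessions over 12 weeks | 1 × 12 = 12 | 3 × 12 = 36 |
| Total exposure | 12 × 60 = 720 minutes | 36 × 20 = 720 minutes |

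Total treatment time is equal, but everything a participant can observe differs. The number of attendances alone (12 against 36) separates the arms. No dummy procedure, screen or matched schedule is described. The answer is yes.

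**2. Could the sentence mean blinding to the hypothesis only?** That is the most the design could offer, but it is not what Section 2.6 says. The section refers to group assignment, and provides that a participant who withdraws is then given her treatment assignment. That provision treats the assignment as unknown to her until then.

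**3. Is assessor blinding shown to fail?** Two routes were checked.

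- *Skin marks.* Section 2.7.2 says: "When moxibustion occurs, there is a slight red burning heat in the" treated area. It describes redness during the session and does not say how long it lasts. The article does not say how assessment visits are timed relative to sessions. The gentle arm also heats abdominal points, at 45 ± 2 °C against 43–45° in the harmonization arm, so redness near the tape is not exclusive to one arm. Treatment ends at week 12, so the week 18 and 24 measurements are well clear of any session.
- *Case report forms.* Assessors alone have access, and local skin events are recorded there. No section says that the forms hold allocation or session records, and burns can occur in either arm.

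Neither route is closed by a stated safeguard, and neither is demonstrated.

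**4. Do the sections on records fit together?** Not fully. Section 2.6 lists a data recorder as a role separate from the assessor, while Section 2.10 restricts the forms to assessors. Section 2.12 puts treatment-related skin events in those forms, and Section 2.13 has the blinded assessors judge safety.

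**5. Size.** The article gives no measurement error, no bias parameter and no information on differential effort. Any shift in centimetres would be an assumption, so none is used here.

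**The case against.** The strongest reply is that the damage is narrow. The article never calls the trial double-blind. Sections 2.6 and 2.13 already describe blinded assessors and a blinded statistician. The primary outcome is a tape measurement by a trained doctor, not a self-report. Both arms receive active moxibustion with the same lifestyle programme, so a difference in diet or exercise effort is conjecture. The scales most exposed are secondary, and the article does not say who scores the Kupperman and TCM scores. All of this stands. It limits the consequence but does not rescue the sentence on participants.

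It might also be said that a woman told only that she will get one of two named treatments may not know which name fits hers. The consent content in Section 2.3 makes that unlikely. Even if it were so, she would be blind to a label and not to the procedure.

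A reader might go further and infer that assessor blinding is broken, because one arm reddens the skin where the tape is placed and because assessors hold the forms that record burns. The documents do not support that. Redness is reported only during treatment, both arms heat the abdomen, and the forms are not said to reveal allocation. The order of visits and the layout of the forms are also details that an article commonly leaves to the full protocol.

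A reader might likewise scale an assumed tape shift against the difference detectable with the 96 per group in Section 2.9. The shift would be invented, and whatever 96 per group can detect says nothing about how large a blinding bias would be.

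**Conclusion.** The statement that participants are unaware of their assignment throughout is wrong for this design. The conclusion rests only on the regimens as described and on the absence of any sham or masking in the article. Participants can be blind at most to which arm is favoured. Bias protection is therefore overstated for IWQOL-Lite and SF-36, and for the symptom scores as far as they are self-reported. For waist circumference, an indirect effect through lifestyle effort is possible but not shown.

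Assessor unblinding remains a possible risk. The size of any bias cannot be estimated from the document. The correction should be made, because it changes how the secondary results may be read. It does not invalidate the primary comparison.

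**What to change.** 1. Replace the sentence in Section 2.6 with a statement that the trial is assessor- and statistician-blinded and that participants are not blinded to the procedure. If it is true, add that they are not told which arm is expected to do better.
2. State that IWQOL-Lite, SF-36 and any self-reported symptom scores are unblinded outcomes and will be interpreted as such. Say who completes the Kupperman and TCM scores.
3. Have the blinded assessor measure the waist before any moxibustion session on the same day, and ask participants not to reveal their treatment.
4. Reconcile Sections 2.6, 2.10, 2.12 and 2.13 on who may see treatment-related records and who assesses safety. Simply hiding adverse-event pages from the assessors would conflict with Section 2.13, which gives them the safety judgement, so the choice should be made explicitly.

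The cost is protocol wording and the order of procedures within a visit. No extra staff, attendances or participants are needed. The price is a less favourable, but accurate, description of the blinding.
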